## Outcomes

### Primary outcome

Gastrointestinal Quality of Life Index (GIQLI) - difference between 0 months and 6 months from randomisation.

### Secondary variables

1. Gastrointestinal Quality of Life Index (GIQLI) at 12 months, 24 months, 48 months and 96 months of randomisation.
2. SF-36 quality of life survey score at 6 months, 12 months, 24 months, 48 months and 96 months from randomisation.
3. Recurrence of diverticulitis and Hinchey class.
4. Undergoing emergency surgery due to diverticulosis / diverticulitis.
5. Undergoing elective sigmoid resection (conservative treatment group).
6. Complications of elective sigmoid resection.
7. Mortality (for any reason in both groups).
8. Complications of diverticulosis (fistula, stricture).
9. Stoma (permanent / temporary).

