The main objective of the study is to investigate the effect of elective sigmoid resection on gastrointestinal quality of life by comparing surgical treatment to conservative treatment in a randomized prospective multicenter study. The secondary objective is to investigate recurrence, mortality, and surgical complications of diverticulitis.

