## Intervention

### 1. Elective laparoscopic sigmoid resection

The patient is scheduled for elective laparoscopic sigmoid resection. Surgery is performed within a maximum of 3 months of randomisation. CRF # 3 is filled just before surgery (e.g., during a preoperative visit). CRF # 2 is filled as the patient is discharged after elective sigmoid resection. After the operation, the patient is given lifestyle instructions as well as a recommendation for the use of a fiber supplement.

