## Statistical analysis plan (amendment 5th Aug 2020)

Primary outcome and continuous secondary outcomes that are normally distributed will be compared using t-test and effect size will be reported as mean difference with 95% confidence interval (95%CI). Continuous secondary outcomes that were not normally distributed will be compared using Mann-Whitney U test and effect size will be reported as  $r (=Z/\sqrt{N})$  without 95%CI. Categorical secondary outcomes will be compared

using Fischer's exact test (if expected cases in one cell <5) or  $\chi^2$  test and effect size will be reported as odds ratios (OR) with 95% CIs. All outcomes will be analyzed using intention-to-treat principle where patients are analyzed in the group where they were randomized to.

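### Operative complications count only after elective resection, so morbidity after emergency surgery is in no outcome and the by-arm comparison of item 6 is unbalanced against surgery

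*Supplement*

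**What the plan says.** In the Supplement, under Secondary variables, item 6 is "Complications of elective sigmoid resection". It is the only outcome concerned with complications of an operation. Item 4, "Undergoing emergency surgery due to diverticulosis / diverticulitis", records that the event happened and nothing about its aftermath.

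The objectives paragraph that follows Background is wider: "The secondary objective is to investigate recurrence, mortality, and surgical complications of diverticulitis". The Finnish text has the same two features. Its objective refers to surgical complications in general, and its item 6 is confined to those caused by elective resection. The restriction is therefore not a translation slip.

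The Statistical analysis plan (amendment of 5 August 2020) tests categorical secondary outcomes with Fisher's exact or chi-squared test, reports odds ratios with 95% confidence intervals, and adds: "All outcomes will be analyzed using intention-to-treat principle where patients are analyzed in the group where they were randomized to". No item is exempted.

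On data capture, the Intervention section says: "CRF # 2 is filled as the patient is discharged after elective sigmoid resection". The Finnish section on parameters to be collected also ties this form to the electively operated patient. No matching discharge form is described for emergency operations. CRF #3 is completed in both arms at every follow-up time point from the questionnaire and a check of patient records (Follow-up section). Its content is not shown.

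**The concern.** A secondary harm outcome should give both randomised strategies the same opportunity to register the event. Item 6 does not, because it is defined by an operation that one arm is assigned to have and the other is asked to avoid. The Conservative treatment section asks for at least 6 months of conservative care before referral for elective resection, unless an absolute indication appears. Early conservative-arm counts are therefore close to zero by protocol.

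The Background section describes emergency resection as the usual consequence of peritonitis, and avoidance of complicated disease as one past reason for elective surgery. The morbidity of that emergency operation belongs in a comparison of the two strategies, yet it is not in the list. At stake is whether the trial can report surgical complications like for like, as its secondary objective implies. The primary outcome, change in GIQLI at 6 months, is untouched.

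**Working it through.** The plan states no figure for this outcome, so there is none to reproduce. The check has a textual part and an illustration of scale.

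**Who can have the event under item 6**

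| Event | Surgical arm | Conservative arm | Listed outcome |
|---|---|---|---|
| Complication of elective resection | all operated as assigned | crossovers only | item 6 |
| Emergency surgery took place | yes | yes | item 4 |
| Non-fatal complication after emergency surgery | possible | possible | none |
| Recurrence and Hinchey class; death; fistula or stricture; stoma | yes | yes | items 3, 7, 8, 9 |

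The third row is the gap. It is open in both arms. If the trial's hypothesis of fewer recurrences after resection is right, it should matter more in the conservative arm.

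**Scale, on assumed rates**

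The documents supply only the planned total of 133, or about 66 per arm. Everything else is an assumption:
- s, complication risk of elective resection: 10–20%
- x, crossover to elective resection in the conservative arm: 0–20%
- e, emergency surgery in the conservative arm: 2–10%
- c, complication risk given emergency surgery: 30–50%

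Risk difference (surgical minus conservative) for item 6 as written: s − x·s.

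With conservative-arm emergency complications added, and no patient counted twice: s − (x·s + e·c).

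The shift is e·c:
- smallest: 0.02 × 0.30 = 0.006, or 0.6 points; 66 × 0.006 = 0.4 patients
- largest: 0.10 × 0.50 = 0.050, or 5.0 points; 66 × 0.050 = 3.3 patients

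Two worked cases:
- s = 10%, x = 0, e = 10%, c = 50%: 10.0 points becomes 10.0 − 5.0 = 5.0 points
- s = 20%, x = 20%, e = 2%, c = 30%: 20 × 0.8 = 16.0 points becomes 16.0 − 0.6 = 15.4 points

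**Counting emergencies in the surgical arm too**

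If e_s is the emergency-surgery risk in that arm and c is the same, the shift becomes (e − e_s)·c. With e = 10%, c = 50% and e_s assumed to be half of e, it is (0.10 − 0.05) × 0.50 = 2.5 points. With e_s = e it is zero.

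**Against sampling error**

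For 10% versus 0% with 66 per arm, the large-sample 95% half-width is 1.96 × √(0.10 × 0.90 / 66) = 0.072, or 7.2 points. The whole assumed range of shifts lies inside that.

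**The case against.** The strongest reply is that item 6 is a safety description of a procedure and was never meant as a contrast between arms. Item 5 is restricted to the conservative group, so the list already holds one item with no between-arm comparison, and the SAP sentence is generic. This is a fair reading of intent, but the plan does not state it. If it is right, no outcome compares surgical complications between arms. If it is wrong, the comparison is unbalanced. The objective is not met in either case.

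A reader might infer several stronger things that the documents do not support:
- *That harms of conservative care go uncounted in general.* Items 3, 4, 7, 8 and 9 count most of them in both arms, including disease severity through the Hinchey class.
- *That item 6 counts only the surgical arm.* It has no arm restriction, and conservative-arm crossovers contribute under intention to treat. The imbalance should therefore shrink as follow-up lengthens.
- *That a 6-month odds ratio with an empty cell is planned.* Items 3 to 9 carry no time point. An empty cell would leave the sample odds ratio undefined, but Fisher's exact test would still run.
- *That the objective expressly names both strategies.* It says surgical complications and no more.
- *That the data are not collected.* CRF #3 may already hold them, and its content cannot be judged from what is shown.

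It is also true that the shift may be small beside sampling error, and that this is one of nine secondary outcomes. That limits the weight of the point. The expected direction can still be foreseen from the definition.

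**Conclusion.** The point holds in a limited form. Operative complications are an outcome only after elective resection, non-fatal morbidity after emergency surgery is in no outcome in either arm, and the definition is narrower than the secondary objective. Applying the SAP as written to item 6 gives a comparison unbalanced against surgery, most strongly early in follow-up.

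The size is unknown because the documents give no rates. The illustrative range of 0.6 to 5 percentage points rests entirely on assumed rates and treats the surgical arm as free of emergency operations, so it is an upper view of the shift. The 5-point end needs the highest assumed emergency rate together with the highest assumed complication rate. The change is worth making because it is cheap and serves a stated objective, not because the main result depends on it.

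**What to change.** - Define the between-arm outcome as complications of any surgery or invasive treatment for diverticular disease, elective or emergency. Grade them on one named scale, count from randomisation over the same stated period in both arms, and use all randomised patients as the denominator.
- Keep complications of elective resection as a descriptive item among operated patients. State in the SAP that this item is not tested between arms.
- Take the data from the record check that already feeds CRF #3 at each time point. Add fields only if the form lacks them.

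The cost is one outcome definition, a short SAP amendment and slightly more record abstraction. Sample size and the primary analysis do not change.

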## Follow-up

The attached flow chart shows patient randomisation, timing of treatment procedures, and follow-up.

Patients are called by phone 6 months after randomisation to inquire about well-being and a decision can be made on a possible change in treatment (a patient in the conservative treatment group can be referred for elective sigmoid resection).

Patients are also monitored by mailed questionnaires (SF-36, GIQLI, and a questionnaire prepared by researchers, see appendix) just before surgery (preoperative visit, etc.) and 6 months, 12 months, 24 months, 48 months, and 96 months after randomisation. The same questionnaires are also completed just before elective sigmoid resection. If there is any ambiguity in the answers to the questionnaire, the researcher will, if necessary, contact the patient by telephone to clarify the ambiguities.

The researcher at each center collects a questionnaire from his or her own center and also checks the entries in the patient records in his or her own area. Based on these, the researcher fills out a CRF # 3 form, which is therefore completed at each follow-up time point.

## Costs

The study is not expected to incur significant additional costs, as elective sigmoid resection is already a normal treatment and inclusion criteria follow general treatment recommendations. The only costs come from the phone call made to the patient (at 6 months) and the postage costs of the questionnaires.

Research may even save hospital costs, as half of patients are randomized to conservative care and no surgical costs are involved.

## Parameters to be collected

Case Report Form (see appendix). Case report form # 1 is completed at the time of randomization (outpatient visit). Case report form # 2 is completed electronically when the patient is discharged. Case report form # 3 is completed at each follow-up time point (just before surgery (preoperative visit, etc.), 6 months, 12 months, 24 months, 48 months, 96 months).

## The sample size

In previous publications, preoperative GIQLI has been 95-100 (SD 22) and postoperative GIQLI 112-114 (SD 19-22) (Forgione et al., 2009; Pasternak et al., 2011). The sample size calculation was made using these values, and the study aims to show a difference of 12 GIQLI points, the standard deviation being assumed to be 22 points in both groups. Using 0.05 alpha, 0.9 power, and 1: 1 allocation, a sample size per group of 60 patients is obtained. The sample size calculation was performed using G \* Power 3.1.5.1 (comparison of means, two-tailed, A priori). Approximately 10% of patients are estimated to disappear at follow-up, bringing the final sample size to a total of 133 patients.

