## **Background**

Diverticulosis is an increasingly common ailment in the aging population. An estimated 25% develop acute diverticulitis (Biondo et al., 2012). The prognosis of acute diverticulitis is related to its severity measured according to the Hinchey classification. The mildest diverticulitis heals on its own, while mortality from diverticulitis that causes fecal peritonitis is high (Wasvary et al., 1999). Peritoneal inflammation caused diverticulitis usually leads to an emergency sigmoid resection and possible intestinal contents diversion

through the stoma. In contrast, milder forms of acute diverticulitis are usually treated conservatively with an intravenous antibiotic and abscesses are drained.

It has previously been recommended that patients with recurrent diverticulitis undergo elective sigmoid resection to avoid further problems with complicated diverticulitis (Rafferty et al., 2006). However, retrospective work has found that the most difficult diverticulitis episode is usually the very first one, and the occurrence of complicated diverticulitis decreases with the recurrence of diverticulitis (Chapman et al., 2006; Ritz et al., 2011). Second, elective surgery for complicated diverticulitis (e.g., abscess) has been recommended (Rafferty et al., 2006). However, this recommendation has also recently been questioned (Gaertner et al., 2013). On the other hand, elective sigmoid resection has been shown to improve quality of life in selected patients with either recurrent diverticulitis or complicated diverticulitis (Forgione et al., 2009; Pasternak et al., 2011).

Current knowledge of who should have elective sigmoid resection is very limited, is based on retrospective comparative series or prospective studies that lack a control group. To date, no randomized, prospective study comparing surgical treatment to conservative treatment in patients with a relative indication (recurrent diverticulitis, complicated diverticulitis, pain after acute diverticulitis) to elective sigmoid resection has been published. An extensive recent treatment recommendation for diverticulitis cannot provide definitive recommendations for the selection of patients for elective sigmoid resection due to the lack of randomized work (Andersen et al., 2012).

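### The 12-point target comes from before-after gains in operated patients and is not justified as a between-arm difference; even at 12 the planned size gives 84% power, not the stated 90%

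*Supplement*

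**What the plan says.** The section on sample size (Supplement, latest English protocol) quotes GIQLI from earlier publications: 95-100 with SD 22 before surgery, and 112-114 with SD 19-22 after it. It continues: "The sample size calculation was made using these values, and the study aims to show a difference of 12 GIQLI points", with an SD of 22 assumed in each group. The result is given as "Using 0.05 alpha, 0.9 power, and 1: 1 allocation, a sample size per group of 60 patients is obtained", and the method as "comparison of means, two-tailed, A priori" in G*Power. An allowance of about 10% for loss to follow-up brings the total to 133.

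The primary outcome is the GIQLI "difference between 0 months and 6 months from randomisation". The statistical analysis plan of August 2020 compares it between the arms by t-test, reports a mean difference with a 95% confidence interval, and adds: "All outcomes will be analyzed using intention-to-treat principle".

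The Background cites the same two publications for better quality of life after resection in selected patients. It says that current knowledge about whom to operate on "is based on retrospective comparative series or prospective studies that lack a control group".

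The documents state no expected conservative-arm change and no minimal important difference, and they do not explain how 12 was chosen.

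**The concern.** The only stated basis for the 12 points is a set of scores before and after surgery in people who were all operated on. The trial tests a different quantity: the change in everyone randomised to surgery minus the change in everyone randomised to conservative treatment. Any gain in the conservative arm, whether from advice and fibre, natural recovery or regression to the mean, is subtracted from the surgical gain. The plan does not say whether 12 is meant before or after that subtraction.

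The 90% also needs checking for its own sake. If it is wrong even when 12 is accepted as the between-arm difference, the protocol claims a property that the design lacks. A non-significant result could then be read as firmer evidence against surgery than a trial of this size can give.

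**Working it through.** **Inputs, all from the sample-size section:** difference 12, SD 22 in each group, two-sided alpha 0.05, power 0.90, allocation 1:1, stated answer 60 per group, about 10% loss, total 133.

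**1. The plan's own figure.** Normal approximation, n per group = 2(z₁₋α/₂ + z₁₋β)² SD²/difference²:
- Two-sided: 2 × (1.960 + 1.282)² × 22²/12² = 70.6, so 71. The exact t calculation, which is the G*Power equivalent, gives 71.6, so 72.
- One-sided 0.05: 2 × (1.645 + 1.282)² × 22²/12² = 57.6, so 58. The exact t calculation gives 58.3, so 59.

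The stated 60 is not reproduced with the two-tailed test; it lies close to the one-sided answer. The loss allowance does reproduce: 120/0.9 = 133.3. The same allowance on 72 per group gives 144/0.9 = 160.

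**2. Power at 60 per group.** Standardised difference 12/22 = 0.545; noncentrality 0.545 × √(60/2) = 2.99. Two-sided power from the t calculation is 84.2% (one-sided 90.8%). Reaching 90% two-sided with 60 per group needs a true between-arm difference of about 13.1.

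**3. What the quoted scores imply.** The smallest gain is 112 − 100 = 12 and the largest is 114 − 95 = 19. The conservative-arm gain compatible with a net difference of 12 is the surgical gain minus 12:

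| Surgical gain | Conservative gain that leaves 12 |
|---|---|
| 12 | 0 |
| 14 | 2 |
| 17 | 5 |
| 19 | 7 |

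**4. Power by net difference** (60 per group, SD 22, two-sided 0.05, t-test). The documents give no conservative-arm change, so the net difference is an assumption shown as a range:

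| Net difference | Power | n per group for 90% |
|---|---|---|
| 12 | 84.2% | 72 |
| 10 | 69.5% | 103 |
| 8 | 50.6% | 160 |
| 6 | 31.6% | 284 |

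If the surgical gain is 12, these rows correspond to conservative gains of 0, 2, 4 and 6. If it is 19, conservative gains of 4, 6 and 7 leave 15, 13 and 12, with power of 95.9%, 89.4% and 84.2%.

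**5. Which SD.** The 22 describes scores at one time point, while the primary outcome is a change. With equal SDs at both times, SD of change = 22 × √(2(1 − r)), where r is the baseline-to-6-month correlation. The documents do not give r, so these are assumed values:

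| r | SD of change | Power at 12 | Power at 10 |
|---|---|---|---|
| 0.3 | 26.0 | 71% | 55% |
| 0.5 | 22.0 | 84% | 70% |
| 0.7 | 17.0 | 97% | 89% |

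The table in step 4 therefore holds for a change score only if r is about 0.5.

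**The case against.** A reader might infer that the stated power holds only if the conservative arm does not improve at all. The documents do not support that, for two reasons. First, the protocol never says that 12 is 112 minus 100. The quoted scores allow surgical gains up to 19, so 12 could already contain a discount of up to 7 points for improvement in the conservative arm. Second, 90% is not reached at a net difference of 12 even with no conservative gain.

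The plan has further answers:
- It already uses 12 in a two-group comparison of means, so the number does serve as a between-group target. This stands, but it does not supply the missing justification.
- Surgery is scheduled within 3 months of randomisation, and before 6 months conservative-arm patients may be operated on only for absolute indications. The documents therefore give no figure for dilution by month 6, and none is used here.
- Advice and fibre are also given to the surgical arm after operation, and one inclusion group must have had symptoms for more than 3 months. Both weaken the case for a large gain confined to the conservative arm. They do not show that the gain is nil.
- Reporting a mean difference with a 95% confidence interval limits how far a null result can be misread. That helps interpretation but does not correct the stated power.
- Power depends on an unstated correlation and could exceed 90% if that correlation is high. This is fair, but the plan makes no such argument and assumes an SD of 22.

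**Conclusion.** The point holds in two parts. First, the target of 12 equals the smallest before-after gain implied by the quoted scores in operated patients. The plan uses it as a between-arm difference without stating a conservative-arm change or justifying 12 for that contrast. Whether 12 is too optimistic cannot be settled from the documents.

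Second, the stated 90% is wrong on the plan's own inputs, whatever the origin of the 12. The shortfall is about 6 percentage points at 12 (84% against 90%), or 12 patients per group (72 against 60). This part needs no assumption beyond the plan's inputs. The figures at 10, 8 and 6 rest on assumed net differences, and for a change score every power figure rests on a correlation near 0.5.

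**What to change.** In the sample-size section:
1. Label 12 as the assumed difference between the arms in 0-to-6-month GIQLI change.
2. Replace the 90% with the power that 60 evaluable patients per group give under a two-tailed 0.05 test and SD 22: 84% at 12, with about 70%, 51% and 32% at 10, 8 and 6.
3. Note that SD 22 comes from single-time scores and equals the SD of change only if the baseline-to-6-month correlation is about 0.5, which is an assumption.

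This changes wording only. No extra patients are proposed, and the analysis and conduct of the trial stay as they are. The cost is a less favourable stated power.

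### The sample size uses the SD of a single GIQLI score, but the primary outcome is a change score, so 90% power is not established for the planned t-test

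*Supplement*

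**What the plan says.** The protocol (Outcomes, Primary outcome) defines the primary outcome as "Gastrointestinal Quality of Life Index (GIQLI) - difference between 0 months and 6 months from randomisation".

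The statistical analysis plan (amendment of 5 August 2020) states: "Primary outcome and continuous secondary outcomes that are normally distributed will be compared using t-test". The effect is to be reported as a mean difference with a 95% confidence interval. No covariate is named, neither baseline GIQLI nor the inclusion criterion by which randomisation is stratified.

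The sample size section reports from earlier publications that "preoperative GIQLI has been 95-100 (SD 22) and postoperative GIQLI 112-114 (SD 19-22". It then says "The sample size calculation was made using these values", and that "the study aims to show a difference of 12 GIQLI points", with "the standard deviation being assumed to be 22 points in both groups". With two-sided alpha 0.05, power 0.9 and 1:1 allocation it arrives at 60 per group, and at 133 in total after about 10% loss. It mentions no SD of change and no correlation between the baseline and 6-month scores.

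**The concern.** A power statement holds only for the quantity whose variability went into it. Here the SD describes how patients differ at one time point, while the tested quantity is how much each patient changes. These are different spreads, linked by a correlation that the plan does not give. The 90% figure is the only justification for the size of the trial. If the correlation is modest, power for the primary test falls into the 70s or below, and a non-significant result could be taken as evidence of no benefit when the trial had limited ability to detect one. If the correlation is high, the trial is better powered than stated. As written, the reader cannot tell which applies.

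**Working it through.** **Inputs from the sample size section:** difference 12; SD 22 before surgery and 19 to 22 after; two-sided alpha 0.05; 60 per group. **Assumed, because the documents do not give it:** the baseline-to-6-month correlation rho, taken as equal in both groups. Power is from the noncentral t distribution.

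**Step 1: the plan's own figure.** The standardised difference is 12/22 = 0.545. Ninety percent power needs 71.6, so 72 per group (71 by normal approximation). With 60 per group, power is 84.2%. The stated 60 is therefore not reproduced. It would come out with an SD of about 20.1, or approximately with a one-sided test (58 to 59 per group), but the section states SD 22 and two tails. The dropout step is consistent: 120/0.9 = 133.3.

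**Step 2: SD of the change.** SD_change = sqrt(SD0² + SD6² − 2·rho·SD0·SD6). With SD 22 at both times this is 22·sqrt(2(1 − rho)). At rho 0.3 it is 22·sqrt(1.4) = 26.0; at rho 0.7 it is 22·sqrt(0.6) = 17.0.

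**Step 3: power of the unadjusted t-test on change, 60 per group.**

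| rho | SD_change (SD6 = 22) | Power | SD_change (SD6 = 19) | Power |
|---|---|---|---|---|
| 0 | 31.1 | 55% | 29.1 | 61% |
| 0.3 | 26.0 | 71% | 24.4 | 76% |
| 0.4 | 24.1 | 77% | 22.6 | 82% |
| 0.5 | 22.0 | 84% | 20.7 | 88% |
| 0.6 | 19.7 | 91% | 18.5 | 94% |
| 0.7 | 17.0 | 97% | 16.1 | 98% |

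**Step 4: where the mismatch has no effect.** The SD of change equals 22 at rho = 0.5 when both SDs are 22, and at rho = 361/836 = 0.43 when the 6-month SD is 19.

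**Step 5: what 90% requires at 60 per group.** SD_change must be at most 20.1. That means rho of at least 1 − 20.11²/968 = 0.58 with equal SDs, or at least (845 − 20.11²)/836 = 0.53 with a 6-month SD of 19.

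**Step 6: the same trial with ANCOVA.** The residual SD is SD6·sqrt(1 − rho²), which cannot exceed 22 if SD6 is at most 22. Taking SD6 = 22 (and ignoring the few degrees of freedom used by covariates):

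| rho | Residual SD | Power |
|---|---|---|
| 0 | 22.0 | 84% |
| 0.3 | 21.0 | 87% |
| 0.4 | 20.2 | 90% |
| 0.5 | 19.1 | 93% |

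**The case against.** The strongest reply is that the direction of the error is unknown. Around rho 0.5 the effect is nearly symmetric: against 84%, rho 0.3 loses 13 points and rho 0.7 gains 13. **This stands.** A reader might infer from the mismatch that the trial is underpowered, perhaps badly. The documents do not support that, because they give no correlation. Nor do they support saying that 22 is right only at a correlation of exactly 0.5, since the cited postoperative SD goes down to 19.

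A second reply is that the 84% at rho 0.5 has nothing to do with change scores. **This also stands.** With equal SDs the mismatch has no effect there; the shortfall arises because 60 does not follow from the stated inputs. For the same reason, the thresholds in step 5 reflect both problems.

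A third reply is that the endpoint may be a comparison of scores at 6 months, for which a single-score SD is the right kind of input. The Finnish primary-outcome wording can be read literally as a difference at 0 and at 6 months, and the analysis plan never uses the term change score. But the English text, including the version that carries the latest analysis plan, describes a difference between the two times, which is a change. Even on the other reading, power at the stated inputs is 84%.

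Finally, a t-test on change is valid under randomisation, and the reported confidence interval will reflect the observed SD. Both are true. Neither supplies the missing basis for the planning figure.

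**Conclusion.** The point holds as a gap in justification. The plan powers a single-score comparison and tests a change, with no correlation or SD of change to connect them. Power for the planned test at 60 per group could lie anywhere from 55% (rho 0) to 97% or 98% (rho 0.7), depending on a correlation that is assumed here, on a 6-month SD of 19 or 22, and on both groups sharing these values. Whether the true figure is below or above 90% cannot be settled from the documents.

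One part does not depend on the correlation: at the stated difference, SD, alpha and sidedness, 60 per group gives 84%, and 90% needs 72. This is a separate defect. Correcting it alone would still leave an SD for the wrong quantity.

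**What to change.** Make the primary analysis an ANCOVA of 6-month GIQLI on randomised arm, adjusted for baseline GIQLI and the inclusion-criterion stratum. SD 22 then becomes an upper bound on the residual SD under the plan's own inputs. Restate the power for 60 evaluable per group as 84% at rho 0, 87% at 0.3, 90% at 0.4 and 93% at 0.5, and label the correlation as an assumption. ANCOVA does not by itself guarantee 90%, so the restated range should replace the single figure.

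If the t-test on change is kept, replace SD 22 with an SD of change computed over a stated range of correlations, and give the resulting power as in step 3. In either case, say explicitly which variable is analysed.

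The cost is a few sentences in the analysis plan and a corrected power statement. Baseline GIQLI and the stratum are already recorded at randomisation, so no extra patients or data are needed.

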## Randomization

The patient is randomized 1: 1 for either elective sigmoid resection or conservative treatment. Patients are stratified based on inclusion criteria so that there are equal numbers of patients from each inclusion group in both randomization groups. Randomization is done using a computer centrally from the Helsinki University Central Hospital (HUCH). In practice, the person performing the randomisation connects to the HUCH server via the Internet, which provides the researcher with information about the patient's randomisation group. Randomization is performed at an outpatient visit, after the patient has first given written consent to participate in the study. Based on the group, treatment is selected, i.e. the patient is either placed in a surgical queue for elective sigmoid resection or given lifestyle instructions as well as instructions on how to use fiber supplementation. Upon randomization, the patient completes SF-36 and GIQLI quality of life questionnaires. Patients are analyzed according to the intention-to-treat principle according to the original randomization group.

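### The sample-size inputs do not give 60 per group: a 12-point difference, SD 22, two-sided 5% and 90% power need 72, and 60 gives about 84% power

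*Supplement*

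**What the plan says.** The section The sample size in the protocol gives every input that a two-group comparison of means requires.

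- Effect and spread: "the study aims to show a difference of 12 GIQLI points, the standard deviation being assumed to be 22 points in both groups".
- Test: "comparison of means, two-tailed, A priori", run in G*Power.
- Error rates, allocation and result: "Using 0.05 alpha, 0.9 power, and 1: 1 allocation, a sample size per group of 60 patients is obtained".
- Loss to follow-up: "Approximately 10% of patients are estimated to disappear at follow-up, bringing the final sample size to a total of 133 patients".

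The Randomization section confirms equal allocation. The Statistical analysis plan (amendment of 5 August 2020) compares the primary outcome between groups with a t-test and reports a mean difference with 95% confidence interval. It mentions no baseline adjustment and no correlation between baseline and 6 months. The other copies of the protocol in the supplement, one English and two Finnish, carry the same sample-size figures, so neither translation nor text extraction explains them.

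**The concern.** The five inputs and the output cannot all be true. A standardised difference of 12/22 = 0.545 at two-sided 5% and 90% power needs clearly more than 60 patients per group, and the gap is too large to be rounding or a choice of formula.

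This paragraph is the only justification for the size of the trial, and it concerns the primary outcome. The figure of 133 is then the recruitment endpoint, and its midpoint of 66 is the time of the interim analysis (section Schedule, interim analysis and completion of the study). A reader who takes the 90% at face value will give a non-significant result more weight against surgery than the stated assumptions support.

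**Working it through.** **Inputs** (all from The sample size): difference δ = 12; SD σ = 22 in both groups; α = 0.05 two-tailed; power 0.90; allocation 1:1; about 10% loss. The test is the two-sample t-test, which is also the test in the analysis plan.

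**1. Attempt to reproduce 60 per group.**

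Normal approximation: n per group = 2 (σ/δ)² (z₀.₉₇₅ + z₀.₉₀)² = 2 × (22/12)² × (1.960 + 1.282)² = 2 × 3.361 × 10.507 = 70.6, so 71.

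Exact calculation with the noncentral t distribution, d = 12/22 = 0.5455: n = 71.6, so **72 per group**.

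The stated 60 is not reproduced; it falls short by 11 or 12 per group.

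**2. Power of the stated size.** With n = 60 per group the noncentrality is 0.5455 × √(60/2) = 2.988, and the critical t on 118 degrees of freedom is 1.980. Power is **84.2%** (84.8% by the normal approximation). The single-look type II error at 12 points is 1 − 0.842 = 0.158.

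**3. What 60 per group would support at 90% power, two-sided 5%.**
- With SD 22, a difference of 13.13 points.
- With a difference of 12, an SD of 20.11.

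**4. Other settings that might have produced 60.**

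| Setting (difference 12 unless stated) | n per group (t-test) |
|---|---|
| As stated: SD 22, two-sided, 90% | 72 |
| One-sided 5%, SD 22, 90% | 59 |
| Two-sided, SD 20, 90% | 60 |
| Two-sided, SD 22, difference 13.2, 90% | 60 |
| Two-sided, SDs 22 and 19, 90% | 63 |
| Two-sided, SD 19 in both groups, 90% | 54 |
| Two-sided, SD 22, 85% | 62 |
| Two-sided, SD 22, 80% | 54 |

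Every row that lands on or next to 60 changes an input that the protocol states explicitly. Which of them happened, if any, cannot be told from the documents.

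**5. The total.** The inflation step is sound in itself: 2 × 60 / 0.9 = 133.3, given as 133. Starting from 72 it would be 2 × 72 / 0.9 = 160.

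**6. Does the allowance for loss cover the gap?** No. If all 133 patients were evaluable (66.5 per group on average), power would be 87.7%, still under 90%.

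**The case against.** The arithmetic is not in dispute. The best counter-arguments concern how much follows from it.

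*SD 22 may not be the SD of the analysed variable.* The primary outcome is defined as the difference between 0 and 6 months, whereas SD 22 comes from scores at single time points. If change scores are compared, their SD is 22√(2(1 − r)), where r is the correlation between baseline and 6 months. The documents give no r. Over an assumed range, power at 60 per group is:

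| r (assumed) | SD of change | Power |
|---|---|---|
| 0.3 | 26.0 | 71% |
| 0.4 | 24.1 | 77% |
| 0.5 | 22.0 | 84% |
| 0.6 | 19.7 | 91% |
| 0.7 | 17.0 | 97% |

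This stands. True power could lie on either side of 90%, so 84% is the power under the protocol's own assumption and not a known property of the trial. It does not rescue the calculation, which fixes the SD at 22.

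*The interim look alters the error rates.* The protocol would stop on a significant result at 66 patients and gives no adjusted threshold. If both looks used 0.05 (an assumption, simulated with 30 and then 60 evaluable per group), the chance of rejecting at 12 points would be about 86%, with type I error about 8%. So 16% is strictly the single-look figure. The interim rule is a separate matter, and it does not bring power to 90% either.

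*The practical harm is limited.* The result will be reported with a 95% confidence interval, which does not depend on planned power; 84% is respectable; and the error neither biases the estimate nor inflates type I error. All of this is true. It argues for a modest correction, not for leaving a wrong figure in place.

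**Conclusion.** The concern holds. On the stated inputs the requirement is 72 evaluable patients per group (160 in total after 10% loss), against 60 and 133 in the protocol. With 60 evaluable per group, power for 12 points is 84.2% and not 90%, or equivalently the difference detectable with 90% power is 13.1 points and not 12. These figures assume SD 22 for the analysed variable, a two-sided 5% t-test and a single analysis. The inconsistency between inputs and output needs none of those assumptions to be right in practice, since it lies within one paragraph of the current protocol, and the 2020 analysis plan leaves it as it is. The cause is unknown, and none of the candidate explanations should be reported as established.

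**What to change.** Keep the enrolment target and correct the statement. Suggested wording: *With 60 evaluable patients per group, a two-sided 5% t-test has 84% power to detect a difference of 12 GIQLI points, or 90% power to detect 13.1 points, assuming SD 22 in both groups.* If the saved G*Power settings show that another SD, difference or sidedness was used, state that input instead, so that inputs and output agree. The same correction belongs in the Finnish text. The cost is one sentence and a less favourable power figure, with no extra patients and no change to conduct or analysis.

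A different route is to base the 90% on a baseline-adjusted analysis (ANCOVA). With SD 22 the residual SD is 22√(1 − r²), and 60 per group reaches 90% once that is about 20.1 or less, which means r of about 0.41 or more. At an assumed r of 0.3 the requirement would be 66 per group; at 0.5 it would be 54. This route costs more than a sentence: it replaces the t-test in the analysis plan and needs a correlation that the documents do not supply, so that value would have to be justified and labelled as an assumption.
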